## 5.3 Blood sampling

### 5.3.1 Safety

For timepoints see schedule of assessments, page 8.

The following blood samples have to be taken: 2.7 mL EDTA blood for the assessment of hematological parameters, 5.5 mL heparin blood for blood chemistry tests. Test tubes will be provided by the Zentrallabor of the Kantonsspital Basel; handling of the blood samples has to follow the instruction of the Zentrallabor, where the following analyses will be performed:

- Hematology:
  - Hemoglobin
  - Hematocrite
  - Red Blood Cell count
  - White Blood Cell count and differential count
  - Platelet count
- Blood chemistry:
  - ASAT
  - ALAT
  - Alkaline Phosphatase
  - Creatinine
  - CRP

### 5.3.2 Immunology

For timepoints see schedule of assessments, page 8.

10 mL full blood for the analysis of humoral immune responses, and 25 mL EDTA blood for the analysis of cellular immune responses. All blood samples will be processed at the Swiss Tropical Institute. The EDTA blood has to arrive there within 4 hours. ELISA will be performed at Pevion Biotech Ltd., the other assays at the Swiss Tropical Institute.

### 5.4 Concomitant medication/treatment

At each study visit/contact, the investigator should question the subject about any medication taken.

Any immunosuppressants or other immune-modifying drugs or treatments, any vaccine other than the study vaccine(s) and any antipyretics administered at ANY time during the period starting 30 days prior to the first dose of study vaccine(s) and ending one month (minimum 30 days) after the last dose of study vaccine(s) must be recorded in the CRF with trade name and/or generic name of the medication, medical indication, total daily dose, route of administration, start and end dates of treatment.

Any other concomitant medication administered prophylactically in anticipation of reaction to the vaccination must also be recorded in the CRF with trade name and/or generic name of the medication, total daily dose, route of administration, start and end dates of treatment and coded as 'prophylactic'.

### 5.5 Subject withdrawals / dropouts / lost to follow-up

Withdrawals / dropouts will NOT be replaced.

For more information see chapter 9 "Study Completion and Discontinuation"

The subject should be informed of the right to abstain from participation in the study or to withdraw consent to participate at any time without reprisal.

## 6 Study Vaccine(s) and Administration

### 6.1 Origin of vaccine(s)

All candidate vaccines to be used have been developed and manufactured by Pevion Biotech Ltd.

The Quality Control Standards and Requirements for each candidate vaccine are described in separate release protocols/Certificate of Analysis and the required approvals have been obtained.

## 6.2 Investigational Product

The virosome-formulated malaria vaccines PEV 301, PEV 302 and vehicle are supplied in vials. The watery solution is slightly opaque.

### **PEV 301 0.500 mL Lot Nr.: 03PEVXX**

Active substances: 10 resp. 50 µg AMA1 mimetic

Excipients: IRIV, PBS pH 7.4

### **PEV 302 0.500 mL Lot Nr.: 03PEVXX**

Active substances: 10 resp. 50 µg CSP mimetic

Excipients: IRIV, PBS pH 7.4

### **PEV 301 + PEV 302 0.500 mL Lot Nr.: 03PEVXX**

Active substances: 50 µg AMA1 mimetic, 50 µg CSP mimetic

Excipients: IRIV, PBS pH 7.4

### **IRIV 0.500 mL Lot Nr.: 03PEVXX**

Active substances: none

Excipients: IRIV, PBS pH 7.4

The vaccines will be blistered and packed in boxes labeled with "Drug for investigational use only" (see example below):

#### **PEV 001**

50 µg PEV 301

Malaria vaccine

Drug for investigational use only

For i.m. injection

#### **Lot:03PEVXX**

Store at +2 – +8°C

Expiry date: MM.JJJJ

Pevion Biotech Ltd.

## 6.3 Treatment allocation and randomization

Randomization will be computer generated. The investigator will receive envelopes with numbers (1 to 46) corresponding to the sequence of assignment to the study. In the envelope the assignment to the study group will be determined.

The 18 volunteers recruited in October will first be stratified into males and females and then randomized in blocks of 9 (1 block = females, 1 block = males) into 3 groups: Group A (n = 8) will be vaccinated with 10 µg PEV 301, Group B (n = 8) will be vaccinated with 10µg PEV 302, and 2 volunteers will receive virosomes alone (Group F). If it is not possible to have an equal sex distribution, the blocks can be filled with participants of either sex.

5 weeks later again 18 volunteers have to be recruited, they first will be stratified into males and females and then randomized into 3 groups: group C (n = 8) will be vaccinated with 50 µg PEV 301, group D (n = 8) with 50 µg PEV 302, and 2 volunteers will receive virosomes alone (Group F).

5 weeks after the 2nd vaccination of groups C and D 10 volunteers will be randomized in blocks of 5 to either group E (n = 8) receiving the combination of 50 µg PEV 301 plus 50 µg PEV 302 or group F (n = 2) receiving virosomes alone.

| Time          | N  | Dose       | PEV 301 | PEV 302 | PEV 301+302 | virosomes |
|---------------|----|------------|---------|---------|-------------|-----------|
| November 2003 | 18 | 10 µg      | 8       | 8       |             | 2         |
| December 2003 | 18 | 50 µg      | 8       | 8       |             | 2         |
| March 2004    | 10 | 50 + 50 µg |         |         | 8           | 2         |

#### 6.4 Dosage and administration

PEV 301 and PEV 302 will be provided in vials. The vials for each group will be provided in individually labeled boxes.

0.5 mL PEV 301 and PEV 302 vaccines should be administered intramuscularly (i.m.) into the deltoid region of the upper arm. The first application is to be given to left, the second to right and the third to the left arm, respectively. The vaccine should not be injected into the blood vessels. The vaccination site should be disinfected with a skin disinfectant (e.g. 70% alcohol) prior to vaccination. The Investigator should use only the needles provided by the Sponsor.

The subjects will be observed closely for at least 30 minutes after vaccination, with appropriate medical treatment readily available in case of a rare anaphylactic reaction following the administration of vaccines. Any reactions that occur during this time must be recorded by the Investigator in the CRF.

The subjects will be instructed to contact the investigator immediately should they manifest any signs or symptoms they perceive as serious. They have to note any signs or symptoms they notice following the vaccinations, on a diary card provided to them.

#### 6.5 Storage

It is essential that Pevion can be certain that the study vaccines retain their safety and potency for the duration of their assigned shelf life. All vaccines must be stored in a safe and locked place with no access for unauthorized personnel. They must be kept in a refrigerator (+2°C to +8°C) and must not be frozen.

#### 6.6 Method of blinding and unblinding

NA

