| STUDY NUMBER                          |                           | PEV 001                                                                                                                                                                                                                                                                                                                                                                                                                                                                                                                                                                                                                                                                                                                                                                                                                                                                                                                 |
| TITLE OF THE STUDY                    |                           | A phase I single-blind randomized placebo controlled dose escalating study of two virosome formulated anti-malaria vaccine components (PEV 301 and PEV 302) administered alone and in combination to healthy adult volunteers                                                                                                                                                                                                                                                                                                                                                                                                                                                                                                                                                                                                                                                                                                  |

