| PROCEDURE                                  | 
Volunteers will be screened, enrolled and followed by the clinical investigator, PD [name] at the Clinical Research Centre of the Kantonsspital Basel.
 
At the screening-visit (days -7 to -5) and after written informed consent has been obtained, the eligible healthy subjects are randomized to vaccination with either three injections of PEV 301 10 µg (Group A) or PEV 302 10 µg (Group B) or PEV 301 50 µg (Group C) or PEV 302 50 µg (Group D) or PEV 301 50 µg plus PEV 302 50 µg (Group E) or virosomes alone (group F) at days 1(+2), 64(+2) and 183(+2).
 
If possible 23 men and 23 women should be enrolled; however, if it is not possible to have an equal sex distribution, the groups can be filled with participants of either sex.
 
The 18 volunteers recruited in October will first be stratified into males and females and then randomized in blocks of 9 (1 block = females, 1 block = males) into 3 groups: Group A (n= 8) will be vaccinated with 10 µg PEV 301, Group B (n = 8) will be vaccinated with 10µg PEV 302, and 2 volunteers will receive virosomes alone (Group F) 5 weeks later again 18 volunteers have to be recruited, they first will be stratified into males and females and then randomized into 3 groups: group C (n = 8) will be vaccinated with 50 µg PEV 301, group D (n = 8) with 50 µg PEV 302, and 2 volunteers will receive virosomes alone (Group F).
 
5 weeks after the 2nd vaccination of groups C and D 10 volunteers will be randomized in blocks of 5 to either group E (n = 8) receiving the combination of 50 µg PEV 301 plus 50 µg PEV 302 or group F (n = 2) receiving virosomes alone.
 
Immunogenicity assessments for humoral immune response are made at baseline (screening blood sample on days -7 to -5), on the days of the 2nd and 3rd vaccination (pre-vaccination samples) as well as 21 (+5) days after each vaccination.
 
Cell mediated immune response will be assessed in groups C, D, E and F only, at baseline (during screening), and 21 (+5) days after each vaccination.
 
Safety assessments are made by the investigator at baseline (before the 1st immunization) and before the 2nd and 3rd immunization as well as 2 (+1) and 7 (+2) days after each immunization.
 
After each immunization the volunteers have to remain in the clinic for a 30 minutes period for the assessment of local and systemic reactions.
 
The volunteers themselves have to fill an adverse event report form (diary card) for a 4 day observation period after each vaccination. Health status will be checked before each immunization, and on days 21 (+5) 85 (+2) and 204 (+2).
 
Standard blood chemistry and hematology will be assessed at the screening visit (days -7 to -5), prior to each vaccination as well as 7 (+2) and 21 (+5) days after each vaccination.
 |                     |                                                                                                                                                          |                 |                                          |

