## 3 Study Design

This prospective phase I, single centre, randomized, single blind, placebo controlled, dose escalating study will be conducted in 46 healthy adult volunteers. Eligible study participants will be randomized into six groups: PEV 301 10 µg (group A, n = 8) or PEV 302 10 µg (group B, n = 8) or PEV 301 50 µg (group C, n = 8) or PEV 302 50 µg (group D n = 8) or PEV 301 50 µg plus PEV 302 50 µg (group E, n = 8) or virosomes alone (group F, n = 6).

Study participants will be vaccinated three times, i.e. at days 1, 64(+2) and 183(+2) and followed-up 3 times after each vaccination. If any of the study groups does not show any immune response 3 weeks after the 2nd vaccination, no 3rd vaccination will be given to that group, i.e. the study for that group will be terminated 3 weeks after the 2nd vaccination.

Groups C & D (PEV 301 50 µg; PEV 302 50 µg) will be started 5 weeks after the 1st vaccination of groups A, B.

Group E (PEV 301 plus PEV 302) will be started 5 weeks after the 2nd vaccination of groups C and D.

Group F will be distributed and serve as a control in all groups receiving the active product.

The total duration of the study for each participant is 31 weeks, the number of visits is 13.

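### The trial is called single-blind, but Section 6.6 gives no blinding method, and T-cell sampling by group marks the two placebo volunteers in the first cohort

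*Protocol*

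**What the plan says.** The synopsis title reads "A phase I single-blind randomized placebo controlled dose escalating study". Its design row repeats the single-blind label, and Section 3 describes the trial as "randomized, single blind, placebo controlled, dose escalating study will be conducted in 46 healthy adult volunteers". None of these places names the blinded party. Section 6.6, "Method of blinding and unblinding", holds only the entry NA.

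Section 6.3 sets out three cohorts. The first has 8 volunteers on PEV 301 10 µg (A) and 8 on PEV 302 10 µg (B), "and 2 volunteers will receive virosomes alone (Group F). If it is not possible" being how the remaining two are described. The second has C 8, D 8 and F 2. The third has E 8 and F 2.

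On cell-mediated response, the Synopsis (Procedure) says that it "will be assessed in groups C, D, E and F only", at baseline and about 21 days after each vaccination. The Synopsis row on cellular sampling likewise leaves out A and B. In the Schedule of Assessments, the T-cell blood row (25 mL EDTA) carries footnote 3, which exempts the two 10 µg groups and no others.

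**The concern.** A protocol that declares a blind and then marks the method as not applicable contradicts itself. The site has nothing to follow, and a reader of the results cannot tell what was masked. This is trial conduct, so it is not a matter that can be left to an analysis plan.

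The T-cell rule makes it worse in one place. Sampling is set by treatment group, but placebo volunteers are spread over all three cohorts. In the cohort where the active groups are exempt, the draw becomes a marker for placebo.

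Safety and tolerability is the primary objective. Part of the evidence is what volunteers write on a diary card for 4 days after each injection, and pain is graded on what the volunteer reports. Group F is the stated control. A volunteer who works out that the injection held no malaria antigen may report differently, and 2 of only 6 controls are exposed.

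**Working it through.** **Inputs.** Group sizes come from Sections 3 and 6.3. The T-cell groups come from the Synopsis and from footnote 3 of the Schedule of Assessments. Blood volumes come from the Schedule: 5.5 + 2.7 = 8.2 mL for safety, 10 mL for humoral immunology, 25 mL for T-cells.

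**The plan's own totals.** (8 + 8 + 2) + (8 + 8 + 2) + (8 + 2) = 46 volunteers, and F = 2 + 2 + 2 = 6. Both agree with Section 3.

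**What the draw reveals.** Within a cohort, P(placebo | T-cell draw) = number in F ÷ number in groups with T-cell sampling.

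| Cohort | Volunteers | F | With T-cell draw | P(placebo) before | P(placebo) given draw |
|---|---|---|---|---|---|
| 1 (A, B, F) | 18 | 2 | 2 | 2/18 = 0.11 | 2/2 = 1.00 |
| 2 (C, D, F) | 18 | 2 | 18 | 2/18 = 0.11 | 2/18 = 0.11 |
| 3 (E, F) | 10 | 2 | 10 | 2/10 = 0.20 | 2/10 = 0.20 |

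In cohort 1 the absence of a draw is equally informative: P(placebo | no draw) = 0/16 = 0. In cohorts 2 and 3 everyone is sampled and the draw carries no information.

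**How visible it is.**
- At a 21-day visit, A and B give 8.2 + 10 = 18.2 mL and F gives 18.2 + 25 = 43.2 mL.
- Over the full schedule there are 9 safety and 6 humoral samples. A and B give 9 × 8.2 + 6 × 10 = 133.8 mL. F gives 133.8 + 4 × 25 = 233.8 mL.

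**How often.** There are up to 1 + 3 = 4 draws: screening, and 21 days after each of three doses. The Synopsis places randomization at the screening visit, so a difference could show before the first injection. If allocation is not yet known when the screening blood is taken, the difference begins at the first 21-day visit and there are up to 3 such draws.

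**Share of controls.** 2 of 6, one third.

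**The case against.** The strongest reply is that single-blind ordinarily leaves the investigator open, and that in a small descriptive phase I trial a leak touching two volunteers matters little. Several parts of this stand.

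- A reader might infer that no blind works at all. The box example names dose and antigen, and "The vials for each group will be provided in individually labeled boxes", while the investigator receives envelopes that determine the group. These arrangements fit an open investigator, so they do not contradict the label. Nothing says volunteers see the boxes. All products are 0.5 mL with one described appearance, so a volunteer-level blind is feasible; it is simply not described.
- A reader might also infer that the laboratories are unmasked, since "ELISA will be performed at Pevion Biotech Ltd., the other assays at the Swiss Tropical Institute" and the former is the sponsor. That rests on silence. Coding may be covered in laboratory procedures, and its absence here is not an error.
- Staff in a single-blind trial already know the allocation, so the extra tube tells them nothing new. A volunteer learns from it only by knowing the rule or comparing visits. The subject information sheet was not available for this review, so what volunteers are told is unknown.
- No comparison with F is named as primary. Safety is mainly listings and frequency tables, with logistic regression for frequent event types, and the Wilcoxon tests compare doses and E with C or D. Laboratory abnormalities are also safety endpoints. Redness and swelling are graded in millimetres, and solicited reactions count as related by rule, which limits the room for judgement.

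What the reply does not remove is the contradiction between the label and Section 6.6, or the fact that the plan's own sampling separates placebo from active volunteers in cohort 1.

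**Conclusion.** The point holds in two parts. First, the protocol declares a single-blind trial and gives no method of blinding. Second, setting T-cell sampling by group undermines the volunteer-level blind in cohort 1: a draw raises the probability of placebo from 0.11 to 1.00 for 2 of the 6 controls, at up to four visits. The exposed data are chiefly the self-reported reactions. The size of any bias cannot be computed from the document.

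This rests on two assumptions. That no T-cell blood is drawn in A and B is inferred from the footnote's place on the blood sampling row; the text says only that T-cells are not assessed there. And the volunteer must learn the rule or notice the difference.

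It would go too far to say that all 46 volunteers are graded under a failed blind, that assay readings are compromised, or that cohorts 2 and 3 leak through this route. The first describes the declared design, the second rests on silence, and the third is contradicted by the table above.

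**What to change.** 1. Replace NA in Section 6.6 with a statement that the volunteers are blinded and how: product prepared and box label kept out of the volunteer's view, and allocation not disclosed to the volunteer until the end of follow-up.
2. Define T-cell sampling by cohort, not by group: cohorts 2 and 3 including their four F volunteers, none in cohort 1. Amend the Synopsis and footnote 3 of the Schedule of Assessments to match.

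The first change costs only wording and a simple site procedure. The second reduces T-cell controls from 6 to 2 + 2 = 4; the two dropped have no concurrent vaccinated T-cell comparator, so little is lost. Drawing T-cell blood from all 18 in cohort 1 would also close the leak (P back to 2/18 = 0.11), but takes 4 × 25 = 100 mL more from each of 16 volunteers for an assay not planned in them.

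Sending immunology samples under code is a sensible, cheap addition. Masking the investigator is optional. It would also require naming someone to count the trigger for convening the safety board, which Section 9.4 defines by dose and antigen cohort.

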#### 6.7 Vaccine accountability

The investigator has the obligation to fill in the respective forms provided. After approval from Pevion Biotech Ltd. Ltd, both used and unused vaccine vials should be sent back to Pevion Biotech Ltd. for destruction. The destruction may be performed at the study site using locally approved biosafety procedures and documentation.

#### 6.8 Concomitant medication/treatment

At each study visit/contact, the investigator should question the subject about any medication taken.

Any concomitant medication administered prophylactically in anticipation of reaction to the vaccination must also be recorded in the CRF with trade name and/or generic name of the medication, total daily dose, route of administration, start and end dates of treatment and coded as 'prophylactic'.

## 7 Health Economics

Not applicable

## 8 Adverse Events (AEs)

The recording of adverse events is an important aspect of study documentation. It is the responsibility of the investigator to document all adverse events according to the detailed guidelines set out below.

The subjects will be instructed to contact the investigator immediately should the subject manifest any signs or symptoms they perceive as serious during the period extending from performance of the first study procedure up to and including 6 months (minimum 180 days) after the last dose of study vaccine.

### 8.1 Definitions

#### Adverse event:

An adverse event is any untoward medical occurrence in a patient or clinical trial subject administered a medicinal product and which does not necessarily have to have a causal relationship with this treatment.

This includes any noxious, pathological or unintended change in anatomical, physiological or metabolic functions as indicated by physical signs, symptoms and/or laboratory detected changes occurring in any phase of the clinical study whether associated with the study vaccine, active comparator or placebo and whether or not considered vaccination related. This includes an exacerbation of pre-existing conditions or events, intercurrent illnesses, or vaccine or drug interaction. Anticipated day-to-day fluctuations of pre-existing conditions that do not represent a clinically significant exacerbation need not be considered adverse events. Discrete episodes of chronic conditions occurring during a study period should be reported as adverse events in order to assess changes in frequency or severity.

Adverse events should be documented in terms of signs and symptoms observed by the investigator or reported by the subject at each study visit. A medical diagnosis should be added.

Pre-existing conditions or signs and/or symptoms (including any which are not recognized at study entry but are recognized during the study period) present in a subject prior to the start of the study should be recorded in the medical history part of the subject's CRF.

Adverse events, which occur after informed consent is obtained, but prior to vaccination, will be documented in the medical history part of the subject's CRF.

Although not considered as an adverse event, hospitalization for either elective surgery related to a pre-existing condition, which did not increase in severity or frequency following initiation of the study, or for routine clinical procedures (including hospitalization for "social" reasons) that are not the result of an adverse event, must be recorded in the CRF. If the hospitalization arises from a pre-existing condition, or was planned prior to the first vaccination, it should be recorded in the medical history part of the CRF. If it was planned after the first vaccination, it should be recorded in the adverse event page of the CRF. In both cases, it should be recorded as 'Hospitalization (Not an adverse event)', and the relationship to vaccination will be checked "No". These adverse events are not considered as SAE.

